# Fedratinib combined with ropeginterferon alfa-2b in patients with myelofibrosis (FEDORA): study protocol for a multicentre, open-label, Bayesian phase II trial

**DOI:** 10.1186/s12885-024-13383-3

**Published:** 2025-01-10

**Keywords:** Myelofibrosis, Phase II, Clinical trial, Fedratinib, Ropeginterferon alfa-2b, JAK2 inhibition, Bayesian design, Tolerability

## Abstract

**Background:**

Myelofibrosis (MF) is a clonal haematopoietic disease, with median overall survival for patients with primary MF only 6.5 years. The most frequent gene mutation found in patients is *JAK2*^V617F^, causing constitutive activation of the kinase and activation of downstream signalling. Fedratinib is an oral selective JAK2 inhibitor. It has shown activity in MF and is well-tolerated, but combination with other therapies is likely needed to achieve clonal remission. Combining a JAK2 inhibitor with an interferon may be synergistic, as haematopoietic cells are activated from quiescence (a typical kinase resistance mechanism) rendering them more sensitive to inhibition.

Ropeginterferon alfa-2b is a next generation pegylated interferon-α-2b with high tolerability and clinical activity in patients with MF, however, evidence of tolerability and activity in combination with fedratinib is lacking in this setting. The aim of the FEDORA trial is to assess tolerability, safety, and activity of fedratinib with ropeginterferon alfa-2b in patients with MF who require treatment to justify further investigation in a phase III trial.

**Methods:**

FEDORA is a single arm, multicentre, open-label, Bayesian phase II trial to assess tolerability, safety, and activity of fedratinib with ropeginterferon alfa-2b aiming to recruit 30 patients. Patients with *JAK2*^V617F^ positive primary or secondary MF, who are aged ≥ 18 years, have intermediate-1 with palpable splenomegaly of > 5cm, intermediate-2, or high-risk disease according to the Dynamic International Prognostic Scoring System (DIPSS), and who require treatment are eligible. The primary outcome is tolerability, whereby the combination is deemed intolerable in a patient if drug-related toxicities in the first four months of treatment lead to: either drug being discontinued; delays in treatment exceeding 28 consecutive days; or death. FEDORA uses a within-patient dose escalation regimen to ensure each patient reaches a personalised dose combination that is acceptable.

**Discussion:**

FEDORA is using a Bayesian trial design and aims to provide evidence of the tolerability, safety, and activity of combining fedratinib with ropeginterferon alfa-2b upon which the decision as to whether a phase III trial is warranted will be based.

**Trial registration:**

EudraCT number: 2021–004056-42.

ISRCTN: 88,102,629.

**Supplementary Information:**

The online version contains supplementary material available at 10.1186/s12885-024-13383-3.

## Background

Myelofibrosis (MF) is a clonal haematopoietic disease characterised by progressive bone marrow fibrosis, splenomegaly, extramedullary haematopoiesis, anaemia, and constitutional symptoms [1]. MF is predominantly a disease of older age (median 66 years) [2] that can arise de novo (primary MF) or as a complication of essential thrombocythaemia or polycythaemia vera (PV) (secondary MF). The median overall survival of patients with primary MF is 6.5 years [3]. Apart from allogeneic stem cell transplantation, which is only applicable for a minority of younger patients with MF, treatment strategies have historically been palliative and for the most part ineffective.

Genetically, MF is a heterogeneous disease. Mutations have been reported in a number of genes, the most frequent of which is a gain-of-function, recurrent mutation *JAK2*^V617F^, causing constitutive activation of the kinase and activation of downstream signalling via *JAK2* [4]. Furthermore, many patients show activation of the JAK2 signalling pathway in the absence of the *JAK2* mutation, likely caused by mutations indirectly activating the JAK2 pathway, e.g., *MPL*. Inhibitors of JAK2 (JAK2i) have subsequently been developed and integrated into treatment guidelines [5, 6].

Fedratinib is an oral selective JAK2i with higher inhibitory activity for JAK2 than other family members [7]. It has a long half-life (41 h) and is, therefore, suitable for once daily dosing. In an early phase investigation in patients with MF, single agent fedratinib was well-tolerated, with encouraging activity and a reduction in disease burden [8]. Later phase trials also demonstrated spleen volume and symptom responses [9–11]. Despite reports of Wernicke’s encephalopathy, this has been re-evaluated with more detailed follow-up data, and the risk of serious consequences mitigated by thiamine monitoring and replacement [12]. Fedratinib has since been approved by the US Food and Drug Administration for adult patients with intermediate-2 or high-risk MF [13] and by the European Medicines Agency and UK’s Medicines and Healthcare products Regulatory Agency in adult patients with MF.

Despite encouraging results, JAK2i are unlikely to be curative, as clonal markers of disease remain detectable in almost all patients, including those demonstrating a clinical response. Additionally, responses to JAK2 inhibition are highly heterogeneous, ranging from stable/progressive disease (primary resistance) in some to complete resolution of splenomegaly in others. Therefore, combination of JAK2 inhibition with other therapies may induce synergistic responses and increase the chance of achieving clonal remission.

Interferon-α (IFN-α) has been used in the treatment of MF for over 30 years with clinical, haematological, and morphological responses seen [14, 15]. The mode of action remains unclear with pro-apoptotic effects on myeloid progenitors [16], host immune enhancing effects and restoring immune surveillance [17], and having direct effects on the malignant *JAK2*-mutant clone [18] reported. Ropeginterferon alfa-2b is a next generation pegylated IFN-α-2b, that has high tolerability and a longer half-life (allowing two–weekly dosing in general and four-weekly dosing in the maintenance phase), compared with conventional pegylated-IFN-α preparations [19]. Ropeginterferon alfa-2b has been shown to induce significant haematological and molecular responses in PV [20]. Early evidence in patients with pre-fibrotic primary MF indicates ropeginterferon alfa-2b can also induce haematological responses and improve quality of life in this setting [21, 22].

Combining a JAK2i and an interferon may be more effective as a MF treatment as haematopoietic cells are activated from quiescence (a typical mechanism of resistance to tyrosine kinase inhibitors) [23], which may render them more sensitive to inhibition. Combinations of a JAK2i and IFN-α have indeed demonstrated dramatic reductions in splenomegaly, improvement in constitutional symptoms, and reduction in leucocytosis and thrombosis, with tolerable side effects in patients with primary and secondary MF [24–27]. Therefore, the aim of the FEDORA trial is to assess tolerability, safety, and activity of fedratinib with ropeginterferon alfa-2b in patients with MF who require treatment to justify further investigation in a larger phase III trial.

## Methods

### Trial design

The FEDORA trial is a single-arm, open-label, phase II clinical trial in patients with primary or secondary MF that is intermediate-1 with palpable splenomegaly of > 5cm, intermediate-2, or high-risk according to DIPSS [28], and who require treatment. FEDORA will recruit 30 patients across 12 UK centres to establish whether the combination of fedratinib with ropeginterferon alfa-2b is tolerable, safe, and clinically active using a within-patient dose escalation regimen to ensure each patient reaches a personalised dose combination that is acceptable. A trial schema is presented in Fig. 1. The trial uses a Bayesian design to allow a judgement to be made on whether a phase III trial is warranted.

**Fig. 1 Fig1:**
[figure not shown]
FEDORA trial schema. Overview of the FEDORA trial. Up to two dose reductions of fedratinib are permitted. A patient is defined as not tolerating treatment if they discontinue either fedratinib or ropeginterferon alfa-2b due to drug-related toxicity, due to delays in treatment exceeding 28 consecutive days due to drug-related toxicity, or if a treatment toxicity-related death is reported, within four months of starting combination therapy. ALT, alanine transferase; AST, aspartate aminotransferase; Ropeg, ropeginterferon alfa-2b

This trial aims to recruit patients over 18 months*,* with participants followed up monthly for two years.

A list of the FEDORA trial sites can be requested from the FEDORA Trial Office ([contact]). The Standard Protocol Items: Recommendations for Intervention Trials (SPIRIT) checklist is provided as Appendix 1 [29]. The World Health Organization (WHO) Trial Registration Data Set is provided in Appendix 2.

### Patient and public involvement

A patient representative from the patient advisory group, MPN-Voice reviewed and refined the participant-facing documents. As a member of the Trial Steering Committee (TSC) they will assess study conduct throughout the duration of the trial, and will support dissemination of the study results via MPN-voice.

### Patient selection

Patients should be previously untreated with a JAK2 inhibitor or with an interferon alfa, and may be newly-diagnosed patients. Full eligibility criteria for FEDORA are listed in Table 1.

**Table 1 Tab1:** Key patient eligibility criteria for the FEDORA trial

**Inclusion Criteria**
Age 18 or over at trial entry
Confirmed diagnosis of primary (overt) or secondary MF, according to WHO 2016 diagnostic criteria
*JAK2*^V617F^ positive, according to routine local assessment
Require treatment, as clinically determined by local investigator
Intermediate-1 with palpable splenomegaly > 5cm, intermediate-2 or high-risk according to DIPSS
Peripheral blood or bone marrow blasts < 10%
Adequate blood counts • Platelet count ≥ 75 × 10^9^/L • Neutrophil count ≥ 1.0 × 10^9^/L
Adequate organ function: • Creatinine clearance ≥ 30 mL/min (as estimated by the Cockcroft-Gault equation) • Serum bilirubin concentration < 1.5 × ULN • Serum alanine ALT *or* AST concentration < 3 × ULN • No worse than mild liver impairment (Child–Pugh class A is permitted)
ECOG performance score ≤ 2
Willing and able to comply with scheduled visits, treatment plan and other study procedures
Willing and able to provide written informed consent for the trial
**Exclusion Criteria**
Any previous treatment with a JAK2 inhibitor
Any previous treatment with interferon-α
Chemotherapy or biologic therapy within 2 weeks of commencing the trial treatment, or ongoing toxicity relating to prior therapy
Blood thiamine concentration below LLN • Before starting treatment, thiamine should be replenished
Active malignancy treated in the last 2 years, except: • Non-melanoma skin cancer • Carcinoma in situ of the cervix or breast • Incidental finding of prostate cancer (T1a or T1b)
Pre-existing thyroid disease unless controlled with conventional treatment
Uncontrolled diabetes
Autoimmune disease
Presence or history of severe psychiatric disorder, including severe depression, suicidal ideation, and suicide attempt
Severe cardiovascular disease, including uncontrolled hypertension, congestive heart failure (NYHA class ≥ 2), serious cardiac arrhythmia, significant coronary artery stenosis, unstable angina, or recent stroke of myocardial infarction that in the opinion of the Investigator makes the patient unsuitable for the trial
Previous organ transplantation receiving immunosuppression
Evidence of active HIV, hepatitis B, or hepatitis C infection, except: • HIV positive patients established on anti-retroviral treatment, with undetectable HIV RNA, after discussion with the patient’s HIV physician • Hepatitis B core antibody positive patients who are (i) surface antigen negative and (ii) hepatitis B DNA PCR negative, who take prophylaxis as per institutional guidelines
Predicted survival of less than 6 months
Allergy or hypersensitivity to fedratinib or ropeginterferon alfa-2b
Patients who are pregnant or breastfeeding (patients of childbearing potential^a^ must have a negative urine or serum pregnancy test prior to trial entry)
Patients and those with partners of childbearing potential^a^ not willing to use highly effective contraception during and for at least 1 month after discontinuation of therapy

*ALT* alanine transferase, *AST* aspartate aminotransferase, *DIPSS* Dynamic International Prognostic Scoring System, *ECOG* Eastern Cooperative Oncology Group, *LLN* lower limit of normal, *MF* myelofibrosis, *ULN* upper limit of normal

^a^Childbearing potential is defined as a pre-menopausal person capable of becoming pregnant. Patients will be considered post-menopausal if they have had no menses for 12 months without an alternative medical cause. A high follicle stimulating hormone (FSH) level in the postmenopausal range may be used to confirm a post-menopausal state in patients not using hormonal contraception or hormonal replacement therapy. However, in the absence of 12 months of amenorrhea, a single FSH measurement is insufficient

### Screening and consent

Potential patients are identified at haemato-oncology multidisciplinary team meetings at participating hospitals and/or identified on their first presentation with MF, for example through referral to haematology from primary care or on emergency admission to hospital. Patients will be given a FEDORA patient information sheet by the site investigator who will later take written informed consent, if agreed by the patient. Appendix 3 contains exemplar FEDORA trial patient information sheet, with Appendix 4 the informed consent form.

### Interventions

Table 2 provides an overview of a patient’s journey during the FEDORA trial.

**Table 2 Tab2:** FEDORA trial schedule of events

Assessment		Screening (within 60 days of registration)	Fedratinib pre-treatment Up to 3 cycles		Combination treatment					End of treatment visit^b^	
					Cycles 1–2		Cycle 3	Cycles 4 +	Follow-up on treatment		
			Day 1	Day 15	Day 1	Day 15	Day 1	Day 1	(Month indicated)^a^		
Informed consent		x									Follow up 3-mothly after treatment for survival, progression and subsequent treatment
Demographic data and medical history		x									
Clinical & physical assessment (Height^c^, weight, ECOG status, blood pressure, pulse, oxygen sats, respiratory rate, physical examination, fundoscopy^c^)		x	x	x	x	x	x	x		x	
ECG		x									
Pregnancy test^d^		x	x		x		x	x		x	
Laboratory Tests	Haematology^e^	x	x	x	x	x	x	x		x	
	Blast count/percentage^f^	x	x	x	x	x	x	x		x	
	Blood film assessment	x							6, 12, 18, 24		
	Biochemistry^g^	x	x	x	x	x	x	x		x	
	Coagulation^h^	x	x		x		x		6, 9, 12, 15, 18, 21, 24		
	Thiamine (vitamin B1) testing	x	After every 3 months of fedratinib treatment								
	Virology^i^	x									
	*JAK2*^V617F^ assessment^j^	x									
Spleen assessment	Palpation	x	x		x		x	x			
	Ultrasound	x							6, 12, 18, 24		
Bone marrow aspirate and trephine		x							6, 12, 18, 24		
Peripheral blood and serum samples for research, including *JAK2*^V617F^ clone size		x			D1 C2 only		x		6, 9, 12, 15, 18, 21, 24		
DIPSS score		x									
MFSAF		x							3, 6, 9, 12, 15, 18, 21, 24		
Disease response assessment (IWG criteria)									6, 12, 18, 24		
WHO bleeding score		x	x		x		x	x			
Fedratinib administration			Daily throughout the trial								
Ropeginterferon alfa-2b administration					Day 1 and 15 of each cycle, starting from Cycle 1						
Thiamine supplementation			Daily, alongside fedratinib treatment								
Transfusion assessment		x	Monitored continuously								
Concomitant medication			Monitored continuously								
Adverse events		x^k^	Monitored continuously								

*DIPSS* dynamic international prognostic scoring system, *ECG* echocardiogram, *ECOG* Eastern Cooperative Oncology Group, *IWG* internal working group, *MFSAF* myelofibrosis symptom assessment form, *WHO* World Health Organization

^a^Within 14 days of time-points indicated

^b^To be completed 28 days after last dose of protocolised drug

^c^To be performed at screening. An eye examination should be performed immediately/as soon as possible for any patients experiencing a decrease or loss of vision during treatment

^d^For women of childbearing potential, to be performed within 14 days of first dose of study drug, at the start of each cycle of treatment and at the end of treatment visit

^e^Haematology to include: haemoglobin, platelets, white blood count (WBC), neutrophils, lymphocytes, and blast count/percentage. May be ± 3 days prior to the start of each cycle

^f^Blast count/percentage as recorded by routine analyser differential, or manual differential from blood film

^g^Biochemistry to include: albumin, bilirubin, alanine transferase/aspartate aminotransferase, alkaline phosphatase, calcium, creatinine, potassium, glomerular filtration rate, total protein, urea, amylase or lipase, sodium, triglycerides, and cholesterol. May be ± 3 days prior to the start of each cycle

^h^Coagulation to include prothrombin time (PT) *or* PT ratio *or* international normalised ratio (INR) and activated partial thromboplastin time (APTT) *or* APPT ratio

^i^Virology to include hepatitis B, hepatitis C, and HIV

^j^Can have been performed at any point prior to registration

^k^Serious adverse events collected from the point of consent, adverse events from the start of trial treatment

The expected doses of each drug are shown in Table 3. An initial pre-treatment stage of fedratinib monotherapy is followed by combination therapy with ropeginterferon alfa-2b from cycle 1. Consecutive 28-day cycles comprise oral fedratinib taken once daily continuously, and subcutaneous injections of ropeginterferon alfa-2b administered on days 1 and 15 of each cycle.

**Table 3 Tab3:** Doses of fedratinib and ropeginterferon alfa-2b

Cycle number (each 28 days)	Fedratinib	Ropeginterferon alfa-2b
Pre-treatment	400 mg once daily	None
1	400 mg once daily	100 µg every two weeks
2	400 mg once daily	150 µg every two weeks
3	400 mg once daily	200 µg every two weeks
4	400 mg once daily	250 µg every two weeks
5–24	400 mg once daily	250 µg every two weeks

Patients will be treated for up to two years (24 cycles). On completion, patients are expected to revert to treatments routinely available as part of NHS care.

### Dose modifications, delays, and discontinuations

Patients should discontinue trial treatment in the following circumstances:Stopped by an investigator for clinical reasons not related to the study drug treatment.Any unforeseen event which, in the judgement of the investigator, makes further treatment inadvisable.Serious violation of the study protocol, including persistent patient non-attendance and persistent non-compliance.If the patient becomes pregnant or is a patient of child-bearing potential who fails to use adequate birth control.Serious adverse event (SAE) requiring permanent discontinuation of treatment.Development of unacceptable side effects.Confirmed disease progression (spleen size increase from baseline of > 5cm, increase in bone marrow fibrosis, or peripheral blood or bone marrow blasts ≥ 20%).At the request of the patient.

In the event of an overdose of either fedratinib or ropeginterferon alfa-2b, treatment should be paused, the patient closely monitored, and supportive measures provided as necessary. Any overdose with or without associated adverse effects (AEs) or SAEs is required to be reported within 24 h of first knowledge of the event to the Trial Office.

#### Fedratinib

During the pre-treatment stage, a tolerable dose of fedratinib must be established for 28 days (one cycle) before ropeginterferon alfa-2b can be started. Two dose reductions are permitted; to 300mg daily and then to 200 mg daily. Patients who require more than two dose reductions during fedratinib monotherapy should not continue to combination therapy and should be withdrawn from the trial.

The dose modifications for haematological and non-haematological toxicities, and treatment of emergent toxicities and management of Wernicke’s encephalopathy are shown in the Appendix 5. If the adverse reaction that results in a dose reduction is controlled, and the toxicity is resolved for at least 28 days, then the dose level may be re-escalated to one dose level higher per month up to the original dose level. Dose re-escalation is not recommended if the dose reduction was due to a grade 4 non-haematological toxicity, grade 3–4 alanine transferase, aspartate aminotransferase, or total bilirubin elevation, or re-occurrence of a grade 4 haematological toxicity.

Fedratinib should be reduced to 200mg once daily if concomitant treatment with strong CYP3A4 inhibitors cannot be avoided and patients carefully monitored. If the strong CYP3A4 inhibitor is discontinued, fedratinib should be increased to 300mg once daily during the first two weeks, and then 400mg once daily thereafter as tolerated.

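### The fedratinib instruction for stopping a strong CYP3A4 inhibitor conflicts with the re-escalation limits for patients already reduced for toxicity

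*Protocol article*

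**What the plan says.** Table 3 (Interventions) plans fedratinib at "400 mg once daily" in pre-treatment and in every cycle. The Fedratinib subsection under Dose modifications, delays, and discontinuations then gives three sets of instructions.

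- **Finding a dose.** Before the combination starts, "a tolerable dose of fedratinib must be established for 28 days (one cycle) before ropeginterferon alfa-2b can be started". That dose may be below the planned one: "Two dose reductions are permitted; to 300mg daily and then to 200 mg daily".
- **Going back up after toxicity.** The adverse reaction must be under control, and a waiting period applies, worded as "the toxicity is resolved for at least 28 days". The pace of any increase is fixed as well: "the dose level may be re-escalated to one dose level higher per month up to the original dose level". A limit follows: "Dose re-escalation is not recommended if the dose reduction was due to a grade 4 non-haematological toxicity". The same limit covers grade 3–4 ALT, AST or total bilirubin elevation and recurrent grade 4 haematological toxicity.
- **Strong CYP3A4 inhibitors.** "Fedratinib should be reduced to 200mg once daily if concomitant treatment with strong CYP3A4 inhibitors cannot be avoided", with careful monitoring. When the inhibitor stops, "fedratinib should be increased to 300mg once daily during the first two weeks, and then 400mg once daily thereafter as tolerated".

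The third set names absolute doses. It does not refer to the dose held before the inhibitor, makes no exception for patients already reduced, and does not refer back to the second set.

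**The concern.** Patients on 300 mg or 200 mg are within protocol, because the design aims at a personalised tolerable dose. The inhibitor paragraph reads as if every patient came from 400 mg. For a patient who did not, one paragraph restricts an increase or advises against it, and the next directs it.

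An investigator with such a patient has two written instructions and nothing that ranks them. Sites could handle the same situation differently, and a patient could be moved above the dose already established as tolerable without the conditions the protocol sets elsewhere for doing so.

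**Working it through.** No calculated figure in the protocol bears on this point, so the check applies the inhibitor paragraph to each permitted dose and compares the result with the re-escalation paragraph.

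**Inputs.** Planned dose 400 mg (Table 3). Permitted reduced levels 300 mg and 200 mg, dose with an inhibitor 200 mg, then 300 mg for two weeks and 400 mg afterwards (all from the Fedratinib subsection).

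**Formulas.** Reduction on starting the inhibitor = (earlier dose − 200) / earlier dose. Excess after stopping = new dose − earlier dose.

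| Dose before inhibitor | Reduction when inhibitor starts | Weeks 1–2 after stopping (300 mg) | From week 3 (400 mg) |
|---|---|---|---|
| 400 mg | (400 − 200)/400 = 50% | 300 − 400 = −100 mg | 400 − 400 = 0 mg |
| 300 mg, for toxicity | (300 − 200)/300 = 33% | 300 − 300 = 0 mg | 400 − 300 = +100 mg |
| 200 mg, for toxicity | (200 − 200)/200 = 0% | 300 − 200 = +100 mg | 400 − 200 = +200 mg |

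**Comparison with the re-escalation paragraph.**

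- *From 400 mg.* The patient returns to the earlier dose, so there is no conflict.
- *From 300 mg.* The patient ends one level above the earlier dose, 14 days after the inhibitor stops. The re-escalation paragraph would permit one level up if 28 days of resolution had been completed and the toxicity was not a listed one. The conflict therefore arises when the 28 days are incomplete, or when the reduction was for a listed toxicity. Otherwise the difference is between permitting the step and directing it.
- *From 200 mg.* The patient ends two levels above the earlier dose, at 400/200 = 2 times that dose. The first level comes at once and the second after 14 days. The re-escalation paragraph needs 28 days of resolution and then one level per month. Taking a month as one 28-day cycle, the second level comes no sooner than 28 + 28 = 56 days after resolution. Even if the 28 days of resolution were already complete, the second step would come 14 days after the first instead of about 28. After a listed toxicity, neither step is recommended.

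**On starting the inhibitor.** For the 200 mg patient, a reduction to 200 mg changes nothing. This shows that the wording does not fit that patient. It does not show that the resulting dose is wrong.

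**The case against.** The strongest reply is that the paragraphs have different triggers. The re-escalation limits concern reductions caused by an adverse reaction, and the inhibitor paragraph concerns reductions caused by an interacting drug. Its wording presupposes a patient above 200 mg and ends at the Table 3 dose. Read together, the second could simply undo the interaction reduction while the first still governs any toxicity reduction. That is a reasonable reading, but the text does not state it, and the endpoint of 400 mg goes beyond undoing the interaction reduction for anyone who started lower.

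Second, the 400 mg step carries a tolerability proviso, and a patient with documented intolerance of 400 mg is a natural case for it. This has weight for the 300 mg patient, whose only excess is that step. It does not clearly cover the 300 mg step for a patient from 200 mg, and it does not restore the 28-day condition, the monthly pace or the advice against re-escalation.

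Third, the re-escalation wording is itself permissive and contains no prohibition. That is correct, so the conflict is between advice and a directive, not between a ban and a directive.

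Fourth, Appendix 5 (dose modifications) and Appendix 6 (concomitant medication) are not shown and could contain a qualifier. That limits certainty. However, the article sets out the inhibitor rule without pointing to either appendix within that paragraph, so the point concerns what is stated and not an omission.

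**Conclusion.** The point holds as a conflict between two stated instructions, confined to patients whose fedratinib was reduced for toxicity before a strong CYP3A4 inhibitor was started and then stopped. On a literal reading the overshoot is one level from 300 mg and two levels from 200 mg. These are the largest outcomes the text produces, since the tolerability proviso may stop the 400 mg step. The number of patients is not given and is probably a small part of 30. The conclusion assumes that the unseen appendices do not already resolve the conflict.

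Four stronger readings are tempting but unsupported.

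- *That reduced patients in general get no reduction on an inhibitor, or that 200 mg is too high for them.* No change occurs only at 200 mg; a 300 mg patient is cut by a third. The article gives no target exposure or rationale from which to judge 200 mg, and the text can be read as naming the dose to use with an inhibitor.
- *That the primary outcome is distorted.* Under Trial outcomes, failure requires discontinuation of either drug or a delay of more than 28 consecutive days, in each case from drug-related toxicity, or a toxicity-related death, within four months of starting the combination. A route from this instruction to such an event is conceivable, but nothing in the article indicates how often it would occur.
- *That the article is at fault for not saying whether an inhibitor-driven reduction counts as one of the two permitted reductions.* That is detail a condensed article may leave to the full protocol.
- *That the re-escalation limits should prevail.* The text does not rank the two paragraphs, and choosing between them is a clinical decision.

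**What to change.** The sponsor and clinical leads should reconcile the re-escalation and CYP3A4 paragraphs of the Fedratinib subsection for patients already below 400 mg. The text should state which instruction governs those patients when a strong CYP3A4 inhibitor is started and when it is stopped. Appendices 5 and 6 should be checked at the same time so that all places agree. If one of them already settles the matter, a cross-reference in the inhibitor paragraph would be enough.

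The content of the reconciled rule is for the clinical leads; no dose, pace or order of precedence is suggested here. The cost is a wording change to one paragraph, with no extra data, visits or patients.
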